### Purpose, Aims, and Hypotheses

The overall purpose of this study is to adapt to the rural sociocultural context and test the efficacy of a tailored, telephone-based intervention (CARE-HF) to support the physical and mental health of rural veterans by enhancing disease self-management and coping processes. To accomplish this goal, our research aims are to:

Adapt the CARE-HF intervention content to the rural sociocultural context using findings from preliminary qualitative research.Examine the effectiveness of the CARE-HF intervention on study outcomes (HF self-care, HF symptoms, health care utilization, depressive symptoms, anxiety, health-related quality of life, stress, resilience, and coping), process (problem-solving), and antecedent (social support) in a sample of rural veterans with HF (N=100) at baseline and 3, 6, 12, and 18 months from baseline.

Our hypotheses are as follows:

Hypothesis 2a: Increases in HF self-care, health-related quality of life, resilience, coping, and problem-solving will be noted at 3 months from baseline and sustained throughout the 18-month follow-up period.Hypothesis 2b: Decreases in HF symptoms (frequency, severity, and interference with physical activity and enjoyment of life), health care utilization, depressive symptoms, anxiety, and stress will be seen at 3 months from baseline and sustained throughout the 18-month follow-up period.

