### Data Collection

Telephone data collection is conducted by a trained research assistant who verbally asks each item and records participants’ responses in an online HIPAA (Health Insurance Portability and Accountability Act)–compliant Qualtrics database. Data are collected at baseline and 3, 6, 12, and 18 months from baseline. In addition to a sociodemographic and clinical survey (age, gender, comorbidities, education, and HF class), a set of self-report surveys is used to measure the study variables (Table 1). We also collect data on standard Veterans Administration Office of Rural Health metrics.

**Table 1 table1:** Study variables.

Variables		Baseline	3 months	6 months	12 months	18 months

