#### Follow-Up Telephone Sessions

Seven follow-up telephone sessions occur weekly for the first month (sessions 2-4) and then biweekly for the second and third months (sessions 5-8). Each session begins with an evaluation of the previous week’s problem, including the veterans’ perceptions of the effectiveness of the strategies used. If needed, problem-solving guidance is provided or reinforced via verbal feedback from the NI. If the problem improves and no further problem-solving is required, the NI works with the veterans to establish a maintenance plan using rational problem-solving strategies. Veterans then repeat the card sorting task to identify new problems and the iterative five-step, problem-solving process starts over. Both current and new problems are identified by the veterans and examined during each follow-up telephone session. Each follow-up session lasts approximately 30 minutes. Figure 2 provides an overview of the study and associated major activities.

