#### Main Analyses

Multilevel growth curve modeling will be used for the testing of aim 2 or the evaluation of the effectiveness of CARE-HF. For each outcome variable, a series of models will be estimated and compared using incremental fit indices, including the Akaike information criteria and the Bayesian information criteria. The first model is an intercept-only model. Then, a growth curve model with a linear growth component will be estimated. Finally, a model with a quadratic growth component will be tested. The multilevel modeling and restricted maximum likelihood estimation method will be used in R (R Foundation for Statistical Computing) [40]. This method can deal with dropouts and missing data without excluding incomplete cases. In addition to fixed effects, random effects will be estimated.

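### Aim 2 predicts a change by 3 months that is then held, but the planned intercept-only, linear and quadratic curves cannot represent a step followed by a plateau

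*Protocol article*

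**What the plan says.** The protocol article, under Purpose, Aims, and Hypotheses, gives both directional hypotheses the same time pattern. For outcomes expected to rise, the change "will be noted at 3 months from baseline and sustained throughout the 18-month follow-up period". For outcomes expected to fall, it "will be seen at 3 months from baseline and sustained throughout the 18-month follow-up period".

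The timing of treatment fits that pattern. Under Follow-Up Telephone Sessions, the calls are weekly at first, "then biweekly for the second and third months (sessions 5-8". With the initial session, all eight contacts lie within the first 3 months. Data Collection gives the visits: "Data are collected at baseline and 3, 6, 12, and 18 months from baseline".

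Main Analyses assigns the test of aim 2 to multilevel growth curves and lists the series for each outcome: "The first model is an intercept-only model. Then, a growth curve model with a linear growth component will be estimated". A quadratic curve is the third and last member of the series. The models are "compared using incremental fit indices, including the Akaike information criteria and the Bayesian information criteria". How time is coded is not stated.

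**The concern.** The hypothesised mean profile is a change completed by the first follow-up visit and flat afterwards. A straight line imposes the same change per month from 0 to 18 months. A parabola can bend, but it cannot rise over one visit and then stay level over the next three. AIC and BIC can only choose among the shapes offered, so they cannot repair a set in which none is right. Random effects do not help either: with complete data the fitted mean is still a line or a parabola.

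Two conclusions are at stake. One is the size of the effect at the end of the intervention. The other is whether it lasts. The Limitations section says that the long follow-up is there to examine sustainability and to assess whether booster sessions are needed. A late decline, or a late rise, created by the choice of curve would bear directly on that decision.

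**Working it through.** The plan gives no figure of its own on this point, so there is none to reproduce. The check asks what the planned models return when the hypothesis is true.

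**Inputs.** Visits t = 0, 3, 6, 12, 18 months (Data Collection). True mean profile, as a multiple of the sustained effect, y = 0, 1, 1, 1, 1; this is the sharpest reading of the hypotheses. Candidate means: constant, linear, quadratic (Main Analyses).

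**Method.** With complete data, and random effects that lie within the span of the fixed effects, the mixed-model mean equals the least-squares projection of y on the polynomial. These results need no assumption about SD, correlation or sample size.

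**Linear, time in months.** Mean of t = 39/5 = 7.8. Sum of squares of t about its mean = 208.8. Sum of (t − 7.8)y = 7.8. Slope = 7.8/208.8 = 0.0374 per month.
- 3-month change: 3 × 0.0374 = 0.112.
- 18-month change: 18 × 0.0374 = 0.672, still rising.

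**Quadratic, time in months.** Coefficients: intercept 0.2122, linear 0.1743, quadratic −0.0075.
- 3-month change: 0.455.
- Peak: 11.6 months.
- 12 to 18 months: 0.700 − 1.009 = −0.31, a false fall.
- 3 to 18 months: 0.700 − 0.455 = +0.245, where the truth is 0.

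**Fitted change from baseline (truth = 1 at every follow-up visit)**

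| Model | 3 mo | 6 mo | 12 mo | 18 mo |
|---|---|---|---|---|
| Intercept-only | 0 | 0 | 0 | 0 |
| Linear, months | 0.112 | 0.224 | 0.448 | 0.672 |
| Quadratic, months | 0.455 | 0.775 | 1.009 | 0.700 |
| Linear, visit number 0–4 | 0.200 | 0.400 | 0.600 | 0.800 |
| Quadratic, visit number 0–4 | 0.629 | 0.971 | 1.029 | 0.800 |
| 5-level factor, or knot at 3 months | 1 | 1 | 1 | 1 |

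By visit number, the false 12-to-18-month fall is 1.029 − 0.800 = 0.23.

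**A gentler sustained profile.** For y = 0, 0.5, 0.75, 0.95, 1, the quadratic in months gives 0.38 at 3 months (truth 0.50) and falls by 0.05 from 12 to 18 months. By visit number it gives 0.45 at 3 months and does not fall.

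**Which model would be chosen, and how often it misleads.** Random-intercept simulations of the exact step used time in months. The effect (0.3 or 0.5 SD), the correlation (0.5 or 0.7) and the dropout timing are assumptions.
- In 100 to 300 runs per setting with 80 to 100 veterans, AIC chose the quadratic in 79–100% of runs. BIC chose it in 79–98% at 0.5 SD and 32–49% at 0.3 SD.
- The false 12-to-18-month fall in the quadratic was nominally significant in 24–27% of runs at 0.3 SD and 45–68% at 0.5 SD.
- With 80 veterans, correlation 0.5 and 3000 runs, the quadratic's 95% confidence interval covered the true 3-month change in 12% of runs at 0.3 SD and 0.2% at 0.5 SD. For the 5-level factor, coverage was 95%.
- In that last setting, power to detect some 3-month change at 0.3 SD was 73% for the quadratic and 76% for the factor.

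**The case against.** The strongest reply is that the exact step is the least favourable reading. The hypotheses do not say that the whole effect is present at 3 months with no change afterwards, and Expected Outcome speaks only of improvement at all time points. This stands as a limit on size: the gradual profile above is distorted much less.

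The figures also depend on how time is coded. A quadratic in the square root of time would recover 0.869 of the step at 3 months, and one in log(1 + t) 0.914, with late falls of 0.14 and 0.09. The article mentions no such transformation, and the two plain codings, months and visit number, both leave a substantial error.

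A third reply is that contrasts and time coding are normally left to an analysis plan that is not shown. That is fair as to contrasts, and their absence from the article is not the fault here. The model series itself is stated, and the problem lies in what it contains.

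Three stronger readings are tempting, and the documents support none of them:
- A reader might infer that any parabola must rise and then fall. Its turning point can lie beyond 18 months, as with the gradual profile coded by visit number.
- A reader might infer that every planned model would show a false decline. Only the quadratic does; the linear model errs the other way.
- A reader might infer that the trial would miss a true 3-month effect. Relative to the quadratic, power is nearly unchanged. A significant quadratic term, moreover, shows curvature, which a true plateau also has, and is not evidence of decline.

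**Conclusion.** The concern holds. The models named for aim 2 cannot represent the time pattern that the hypotheses state. Under an exact step, the 3-month effect is estimated at 0.11 to 0.20 of its true size by the linear curve and at 0.455 to 0.63 by the quadratic, the ranges running from months to visit number. The linear curve adds a false continuing rise. The quadratic adds a false fall of 0.31 to 0.23 of the effect between 12 and 18 months. These figures assume complete data and a full effect at 3 months; a slower sustained gain shrinks them. The selection, coverage and power results rest on assumed effect sizes and correlations. What is harmed is the estimated 3-month effect and the judgement on durability.

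Health care utilization is a separate case. Table 1 shows no baseline measurement for it, so a baseline-to-3-month change cannot be estimated under any model, although hypothesis 2b includes it.

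**What to change.** Make the main model a mixed model with time as a 5-level factor, which also matches the 5-time-point repeated-measures ANOVA behind the sample size in Design and Sample. A piecewise-linear model with a knot at 3 months is an acceptable alternative and has three fixed effects, as the quadratic does.

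For each outcome measured at baseline, estimate 3 months minus baseline and 18 minus 3 months, each with a confidence interval, and base the conclusion on durability on the second. Keep the linear and quadratic curves as descriptive secondary models, with the coding of time stated.

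For health care utilization, limit the analysis to change across the 3-, 6-, 12- and 18-month visits, and do not claim a decrease from baseline.

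The cost is analysis wording, at most two more time parameters than the quadratic (four instead of two), and slightly more analysis work. The Results section says that analysis will follow study completion, so the change can still be made beforehand.

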### Design and Sample

This study includes a repeated-measures, single-group design. Veterans are recruited from Veterans Administration home-based cardiac rehabilitation clinics, cardiology clinics that serve veterans, veterans-based community resource centers, and social media campaigns using study flyers. Veterans with HF (N=100) will be recruited over 3 years, with the anticipated enrollment of 5 or more veterans per month. The desired sample size was based on a power analysis for repeated-measures ANOVA with 5 time points, α=.05, a medium effect size (f=0.25), and 80% power, plus oversampling for potential attrition (20%) estimated from studies involving patients with HF [17,18]. Veterans are eligible for participation if they (1) have a diagnosis of HF; (2) are aged 18 years or older; (3) have New York Heart Association functional class II-IV HF; and (4) can read, write, and communicate verbally in English, and excluded if they have a history of cognitive impairment.

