#### Covariates

Several covariates will be considered for inclusion: age, biological sex, race and ethnicity, and educational attainment. Only covariates that are statistically significant predictors of at least one outcome will be included. That is, the same covariates will be used in all analyses for the primary aim.

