### Limitations

This study has some limitations. First, enrollment is restricted to rural veterans with HF; therefore, generalization of findings may be limited. Second, this is a single-group study that lacks a comparison group, reducing our ability to make meaningful comparisons across outcomes. Third, a lengthy follow-up period is included to examine the sustainability of the intervention effect and assess the need for booster sessions, but this may also contribute to a higher-than-desired attrition rate. Despite these limitations, this study will provide valuable insights for program evaluation and improvement, as well as intervention adherence and sustainability of effect to inform future research.

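### The plan relies on REML to handle dropout but leaves HF class and comorbidity out of the candidate covariates, so severity-related loss could bias the 18-month sustained effect towards benefit

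*Protocol article*

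**What the plan says.** Main Analyses plans multilevel growth curve models fitted by REML for each outcome and says of them: "This method can deal with dropouts and missing data without excluding incomplete cases". No condition is attached.

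The Covariates section names as candidates "age, biological sex, race and ethnicity, and educational attainment". It keeps only those that significantly predict at least one outcome, and uses the same set throughout. Table 1 also labels social support a covariate. Neither place lists HF class or comorbidities, although Data Collection says the baseline survey records both.

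The setting comes from other sections:
- Design and Sample: "This study includes a repeated-measures, single-group design", in veterans who "have New York Heart Association functional class II-IV HF", with 20% attrition allowed for.
- Data Collection: "Data are collected at baseline and 3, 6, 12, and 18 months from baseline".
- Purpose, Aims, and Hypotheses: the changes at 3 months are to be "sustained throughout the 18-month follow-up period".
- Limitations, on the long follow-up: "this may also contribute to a higher-than-desired attrition rate".

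**The concern.** Likelihood estimation uses the available scores of those who leave, and is valid when the chance of leaving depends only on what the model contains: earlier scores and included covariates. Two kinds of loss fall outside that.

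1. **Loss related to baseline severity.** If veterans in a worse HF class both decline faster and leave more often, and class is not in the model, the later mean drifts towards the healthier veterans who remain. Earlier scores pick up only part of this.
2. **Loss after unseen deterioration.** The last two gaps between assessments are six months each. A veteran can worsen or die in a gap with no score to show it. The Background itself links depression and anxiety, two of the outcomes, to higher mortality and hospitalization.

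Both push the 18-month mean towards benefit. Hypotheses 2a and 2b need that mean to be right, and with one group there is no contrast in which similar losses could cancel. Death adds a question of meaning: the model in effect continues a score trajectory beyond death, where a sustained gain is not defined.

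The covariate list matters because it is a choice the article fixes. Significance for an outcome is the wrong test for a variable whose role is to make the missing-data assumption credible.

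**Working it through.** **The plan's own figures.** Design and Sample bases the sample size on "repeated-measures ANOVA with 5 time points, α=.05, a medium effect size (f=0.25), and 80% power", plus 20% for attrition. With N = 100, the number left is 100 × (1 − 0.20) = 80. N = 100 can be neither confirmed nor refuted, because within-person correlation and sphericity are not given. Correlation 0.5 with full sphericity gives 21, or 21/0.80 → 27 after inflation. Other choices come close to 100: a noncentrality of n(m−1)f² with m = 5 time points and a sphericity correction of 0.5 gives 79, or 79/0.80 → 99. Nothing below depends on this; only the 20% and the 80 are carried forward.

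**Check 1: loss depends on HF class, and class is not modelled.** Assumptions: the 18-month course differs by 0.5 SD between better and worse class, the odds ratio for dropout is 2 to 4, and (for the hand calculation) the two classes are equal in size.
- Write loss as 0.20 + d in the worse class and 0.20 − d in the better one. The odds-ratio condition is (0.20 + d)(0.80 + d) / [(0.80 − d)(0.20 − d)] = OR.
- OR 2 gives d = 0.054; OR 4 gives d = 0.102.
- The worse class's share of completers falls from 0.5 to (0.80 − d)/1.6, a drop of d/1.6. The false benefit among completers is 0.5 × d/1.6.
- OR 2: 0.5 × 0.054/1.6 = 0.017 SD. OR 4: 0.5 × 0.102/1.6 = 0.032 SD.

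A simulation with the same slope difference and odds ratios gives 0.02-0.03 SD at 20% loss and 0.05-0.11 SD at an assumed 50% loss without class in the model. With class-by-time terms the bias is about zero.

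**Check 2: loss depends on the current unseen score or the veteran's own slope.** Inputs: 100,000 simulated patients at the protocol's visits, true mean change zero, scores scaled to a total SD of 1, residual variance 0.51, random-slope SD 0.6 or 0.9 over 18 months, dropout hazard ratio 2 or 3 per SD, and a quadratic growth model fitted by REML. Everything except the visits, the model form and the 20% is assumed.

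| Total loss | False benefit, loss depends on unseen course | Error, loss random or dependent on last observed score |
|---|---|---|
| 20% (stated) | 0.07-0.15 SD | within 0.01 SD of zero |
| 30% (assumed) | 0.11-0.23 SD | within 0.01 SD of zero |
| 40% (assumed) | 0.16-0.32 SD | within 0.01 SD of zero |

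A second simulation under other assumptions (a 0.3 SD gain fading to zero at 18 months, dropout log-odds 0.5-1.0 per SD of the current score) gives 0.03-0.07 SD at 20% loss. The direction is the same and the size about half.

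**Against sampling error.** With 80 evaluable patients, the crude SE of the 18-month change is √[(2 × 0.51 + 0.6²)/80] = √(1.38/80) = 0.13, or √[(1.02 + 0.9²)/80] = √(1.83/80) = 0.15. A bias of 0.07-0.15 SD is therefore about 0.07/0.13 ≈ 0.5 to 0.15/0.15 = 1.0 SE. The one-sided chance of a false finding of benefit rises from 2.5% to about 8-17%.

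**Does the covariate change help?** Fully under check 1. When dropout also depends on the unseen score, including class reduces the bias but some remains. That is why a sensitivity analysis is also needed.

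**The case against.** The sentence on dropout can be read as saying only that incomplete cases stay in the analysis, and that is true. A reader might infer that the stated property is false; the text does not support that. The fault is that a statement about case retention stands as the only answer to dropout.

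A reader might also infer that dropout will bias the result. The documents give no reasons for loss, and deterioration already visible in earlier scores does no harm in the simulations. Telephone assessment and a payment after each completed assessment make it easier for a sick veteran to stay in. Only could, not would, is supported.

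Nor does the article say that high attrition is expected; Limitations raises it as a possibility. The 20% is taken from earlier studies, and the trial described in the Background with the same citations ended data collection at 13 weeks. That is a reason for caution about the figure, not proof of a higher one. A comparator would have offset the bias only if loss were similar in both arms, and its absence is disclosed.

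Finally, a missing-at-random statement, the handling of deaths and a sensitivity analysis may sit in an analysis plan that is not shown, so their absence is not an error here. They belong to the remedy. The covariate list is different, because the article does fix it. All of these objections stand as limits on the claim; none answers the omission of HF class and comorbidity.

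**Conclusion.** The point holds as a weakness in a choice the article fixes. It relies on REML for dropout while restricting the candidate covariates to demographics kept by significance, and leaves out two collected variables that plausibly drive both course and loss. The possible bias in the 18-month change is towards benefit, roughly 0.02-0.15 SD at the stated 20% loss and larger if loss is higher. It is about zero if dropout depends only on observed scores.

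The range rests on assumed dropout strengths, slope variation and class effects; only the 20% comes from the protocol. The upper end is about one standard error with 80 evaluable patients, enough to matter for a sustained-effect claim but not to invalidate the study. The change is worth making: Results places the analysis after study completion, and only 4 veterans had finished by December 2024.

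**What to change.** 1. In Covariates, include baseline HF class and comorbidity in every growth model regardless of significance, with their interactions with time, and report the 18-month change averaged over the baseline mix of the enrolled group.
2. In Main Analyses, add that the estimates assume missing at random given the observed scores and these covariates.
3. Report deaths separately from other loss, by assessment interval.
4. Add a delta-adjusted sensitivity analysis of the 18-month change, in which unobserved scores are made worse over a stated range of shifts. Report it as a qualification of the sustained claim, not as a pass/fail rule.

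The data for item 1 are already collected. With HF class as two indicators and comorbidity as one count, the added fixed effects are 3 × 2 = 6 in a linear growth model and 3 × 3 = 9 in a quadratic one. Beyond that the cost is a little more analysis, and the sustained claim may come out somewhat less favourable.

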#### Covariates

Several covariates will be considered for inclusion: age, biological sex, race and ethnicity, and educational attainment. Only covariates that are statistically significant predictors of at least one outcome will be included. That is, the same covariates will be used in all analyses for the primary aim.

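### Covariates are chosen by a significance screen on the outcome data, from a list that leaves out baseline HF class, comorbidities and social support

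*Protocol article*

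**What the plan says.** The Covariates section of the protocol article gives a closed list: "Several covariates will be considered for inclusion: age, biological sex, race and ethnicity, and educational attainment". It then sets the selection rule, "Only covariates that are statistically significant predictors of at least one outcome will be included", and its scope: "That is, the same covariates will be used in all analyses for the primary aim". No significance threshold is given for the screen.

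Other sections bear on the list:

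- Data Collection describes a "sociodemographic and clinical survey (age, gender, comorbidities, education, and HF class"), so HF class and comorbidities are recorded. Design and Sample requires that participants "have New York Heart Association functional class II-IV HF", so severity varies across the sample.
- Table 1 has a Covariates block with one entry, social support, ticked at baseline only. The aims in Purpose, Aims, and Hypotheses call social support an antecedent to be examined from baseline through 18 months. The Covariates section does not mention it.
- Main Analyses says of the restricted maximum likelihood (REML) multilevel model: "This method can deal with dropouts and missing data without excluding incomplete cases".

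**The concern.** Two features of the rule are badly fixed.

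First, the covariate set is decided by testing candidates against the same outcomes that aim 2 evaluates. One significant result for any outcome puts the covariate into all models. The chance that an irrelevant covariate passes therefore grows with the number of outcomes, and the main model cannot be written down before the data are seen.

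Second, the list is demographic only. This is a single-group study, so change over time is the whole effect estimate, and there is no comparison arm in which attrition bias could cancel. The hypotheses claim change that lasts to 18 months, and Limitations warns that the long follow-up may raise attrition. A likelihood-based model uses incomplete cases validly only if dropout is ignorable given the observed outcomes and the covariates in the model. If baseline severity affects both trajectory and dropout, leaving it out weakens that condition and pulls estimated change towards that of the veterans who stay.

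**Working it through.** The plan attaches no figure to the covariate rule, so there is nothing to reproduce. The planned N of 100 does not bear on it.

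**Inputs.** Four candidates (Covariates). Nine outcomes in Table 1, or ten with problem-solving, which Table 1 lists as a process variable. Planned attrition of 20% (Design and Sample). Assumed: a screening threshold of 0.05, which the article gives as α for the sample size but not for this screen.

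**1. Retention of a noise covariate, independent outcomes.** P(kept) = 1 − 0.95^k.

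- k = 9: 1 − 0.630 = 0.370
- k = 10: 1 − 0.599 = 0.401

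For four independent noise candidates, P(at least one kept) = 1 − 0.95^(4k), which is 0.842 for k = 9 and 0.871 for k = 10. The expected number kept is 4 × 0.370 = 1.48 or 4 × 0.401 = 1.61.

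**2. Correlated outcomes.** Test statistics were simulated with a common correlation r (200,000 draws, two-sided cut-off 1.96).

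| r | kept, 9 outcomes | kept, 10 outcomes | at least one of four kept |
|---|---|---|---|
| 0.3 | 32% | 35% | 79-82% |
| 0.5 | 27% | 29% | 72-74% |
| 0.7 | 20% | 21% | 59-62% |
| 0.9 | 12% | 13% | 41-42% |

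Every scenario exceeds 5%.

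**3. What a noise covariate costs.** In a simulated linear growth model with N = 100, the slope's standard error was 0.086 without a noise main effect and 0.088 with one. That difference is within simulation error.

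**4. Omitting severity.** The model was a generalised least squares growth curve on all available visits, standing in for the REML fit, with 3,000 replicates per row. All of these values are assumed: N = 100, about 17-20% dropout, 40% of veterans in the more severe class, true mean slope −0.30. The severity effects and the log odds ratio of dropout for the severe class are varied.

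| Effect on level | Effect on slope | Log OR, dropout | Slope, severity omitted | Slope, severity and severity-by-time included |
|---|---|---|---|---|
| 0.5 | 0 | 1.0 | −0.305 | −0.297 |
| 0.5 | 0.3 | 1.0 | −0.315 | −0.302 |
| 0.5 | 0.5 | 1.0 | −0.320 | −0.299 |
| 0.5 | 0.5 | 1.5 | −0.338 | −0.300 |
| 0 | 0.5 | 1.5 | −0.331 | −0.300 |

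Bias with severity omitted runs from 0.305 − 0.300 = 0.005 to 0.338 − 0.300 = 0.038. The standard error of the slope was 0.086 to 0.092, so the largest bias is 0.038 / 0.091 = 0.42 standard errors. When severity affects only the level, the bias is negligible. It becomes visible only when severity affects both slope and dropout.

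**5. Social support, side by side.** In Table 1 it is a covariate measured once. In the aims it is an antecedent followed over five time points. In the Covariates section it is absent. The three cannot all describe the same analysis.

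**The case against.** The best defence is that little harm follows. The target is within-person change, and a time-invariant main effect hardly touches the time coefficient (step 3). The model conditions on each veteran's earlier values of the same outcome, which already carry some information on severity, and the simulated bias stays below half a standard error. All of this stands, and it limits the size of the point. It does not justify choosing covariates from the outcome data or excluding severity measures that are already recorded.

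A reader might infer more than the documents support:

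- *That severity is the main driver of dropout.* No section says so. The only contributor to attrition that the article names is the length of follow-up (Limitations). Severity is a plausible predictor, not a documented one.
- *That noise is kept about 80% of the time.* Counting about 31 totals and subscales gives 1 − 0.95^31 = 0.80, but that count sets totals beside their own subscales, which cannot be independent. The rule speaks of outcomes, and Table 1 lists nine.
- *That change is inflated by 0.06 to 0.12 SD.* Such figures come from a completer mean with opposite trajectories by class and 10% versus 40-60% loss in equal halves, hence 25-35% overall. The plan allows for 20% and does not analyse completers only.
- *That concurrent cardiac rehabilitation must be modelled.* The article says "Veterans are recruited from Veterans Administration home-based cardiac rehabilitation clinics". That names a recruitment setting. It does not say that participants were in a programme during the study, or that source is recorded per person.

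The objection that more terms strain the sample also has force. These are person-level covariates, so the relevant number is veterans, not visits. Results reports 56 enrolled in about 20 months. At that pace, six more months give 56 + 6 × 2.8 = about 73. This argues for a short covariate set.

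**Conclusion.** The point holds as a poorly fixed analysis rule, with modest numerical consequences. The screen makes the main model depend on the outcomes and keeps irrelevant covariates more often than the nominal 5%: about 37-40% under independence, falling to 12-13% at correlation 0.9, given the assumed 0.05 threshold. The cost is lost prespecification more than lost precision.

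Excluding HF class and comorbidities makes the ignorability assumption behind the REML analysis less plausible than it needs to be. Under the assumed values the slope bias is about 0.005-0.04 against a standard error of about 0.09. Its true size cannot be known from the article, because neither the causes of dropout nor the trajectories by class are given. The inconsistency over social support is plain on the face of the text and needs no assumption.

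**What to change.** Before any outcome analysis:

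1. Delete the significance screen.
2. Fix a short covariate set for all models: age, sex, race/ethnicity, education, baseline HF class and comorbidities.
3. Reconcile the role of social support across the aims, Table 1 and the Covariates section, then add its baseline value if it is to be a covariate.
4. Add an HF-class-by-time term and report change averaged over the baseline HF-class distribution, so that the estimate refers to the enrolled sample and not to those who remain.
5. State the missing-at-random assumption, conditional on the observed outcomes and these covariates, beside the sentence on dropout in Main Analyses.

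The change needs no new visit. Data Collection lists HF class, comorbidities, age, gender and education, and Table 1 lists baseline social support. Race and ethnicity are not named in that survey list, so their recording should be confirmed. Results says that analysis follows study completion, so the wording can still be fixed in advance. The downside is a few person-level degrees of freedom from at most 100 veterans. A severity term also does not settle how deaths are treated.
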